##### SUCCEAT Intervention group 1—Workshop support groups for carers

All SUCCEAT workshop support groups are held at the Medical University of Vienna, Department of Child and Adolescent Psychiatry, once in a week in the evening (from 6 p.m. to 8 p.m.) and consist of eight weekly workshop sessions (see Table 1). Carers receive the SUCCEAT workbook as a hardcopy and the DVD (The Succeed Foundation, 2011; German translation of our research group) at the first workshop session. The two SUCCEAT coaches present the contents of the SUCCEAT intervention listed in Table 1 with a PowerPoint presentation and support the carers personally during the sessions. In each session, the carers will get a hardcopy handout with a summary of the workshop session. The workshops are designed to be interactive with role plays and group work for the carers. The carers are encouraged to talk about their concerns and experiences with each other. They have time to report their “experiments” and to reflect together.

##### SUCCEAT Intervention group 2—Web‐based support groups for carers

All the carers get to know the two SUCCEAT coaches and the other participating carers of their web‐based support group personally in a welcome meeting at the beginning of the intervention at the Medical University of Vienna, Department of Child and Adolescent Psychiatry, and subsequently complete the programme at home via Internet. The web‐based support groups consist of eight weekly web‐based modules (see Table 1). The SUCCEAT web‐based modules and the SUCCEAT workbook are available on a website within a structured program (http://www.succeat.at). The formal conditions are introduced at the welcome meeting, and the carers receive the DVD (The Succeed Foundation, 2011; German translation of our research group). Carers get access to one new web‐based module weekly. They are instructed how to work on the program at any time. Within the modules, carers fill in interactive fields of the exercises and report on their experiences and the “experiments” they carried out at home. In addition, carers are invited to use the opportunity to contact the coaches via a personal message system on the website. The coaches offer their support and give weekly feedback to the exercises and the “experiments” of the carers via the personal message system. The carers have the additional possibility to communicate with the other carers and to discuss different topics in an unguided online forum on the website. This online forum is controlled regularly by the coaches and the coaches delete disturbing comments.

#### Group 3 Control group—Conventional carers' support and TAU

2.3.2

Carers and patients receive TAU at inpatient and outpatient centres with ED units according to the NICE guidelines (NICE, 2017). Therefore, carers take part in conventional carers' support groups or in other treatments for families (e.g., psychotherapy, medical counselling, and psychoeducation). When patients with AN are weighed at specialist services, the results are shared with their family members or carers (if appropriate). Family members or carers (as appropriate) are included in any dietary education or meal planning for the patients. Psychological treatment of the patients includes some family sessions together with their family members and psychoeducation. The therapy emphasises the role of the family in helping the person to recover. Early in treatment, a good therapeutic alliance with the parents or carers and other family members is established and the parents or carers are supported to take a central role in helping the patients manage their eating. In the second phase, parents and carers help to support the patients to establish a level of independence appropriate for their level of development. The families' concerns are addressed and family members are supported in order to cope with distress.

### Outcome measures

2.4

To describe the sample, clinical data and demographic information about the patients and their carers are collected at baseline (T0; age, sex, educational level, family situation, migration status, and socio‐economic status). Further assessments for the primary and secondary outcome measures (see Table 2) will take place before starting the intervention (T0), after 3 months (postintervention, T1), and 1 year after the intervention (follow‐up, T2). The semistructured interview of the Eating Disorder Examination (Fairburn & Cooper, 1993; German version: Hilbert & Tuschen‐Caffier, 2006) is conducted face‐to‐face or via telephone by professionals (clinical and health psychologists and psychotherapists). These professionals also administer the other questionnaires, which are answered in a paper–pencil version by the carers and patients themselves. These professionals have already been trained to use these measures before this RCT (by experienced professionals in this field) or received training by [name] prior to the study. The questionnaires for the process evaluation are answered by the carers of the SUCCEAT intervention after each workshop session or web‐based module and at T1 and T2. Table 2 and Supplement S1 contain further information about the questionnaires.

### Sample size calculations

2.5

Power analysis was done with G*Power version 3.1.5. In order to detect a difference for the primary outcome (General Health Questionnaire, see Sepulveda, Lopez, Todd, et al., 2008) by calculating repeated measures analysis of variance (ANOVA; if the s*phericity* assumption is not met) at a 5% significance level with 0.88 power, carers of 40 patients per group are needed to detect medium effects (Faul, Erdfelder, Lang, & Buchner, 2007). We expect a dropout rate of about 17% (see Wagner et al., 2015). Therefore, we plan to include the carers of 48 patients per treatment arm, resulting in a total sample size of 144.

### Randomisation

2.6

After recruitment of the patients and their carers (at the Medical University of Vienna, Department of Child and Adolescent Psychiatry, and by consultant child and adolescent psychiatrists in adjacent federal states to Vienna), patients and carers who meet the eligibility criteria give their informed consent, perform baseline assessments, and are randomly allocated to one of the two intervention groups (SUCCEAT workshop support group or SUCCEAT web‐based support group) by our research group at the Medical University of Vienna. Random allocation is made in a blockwise manner in order to keep the sizes of treatment groups similar. Incoming patients are numbered consecutively, and randomisation is done blockwise according to the consecutive numbering, in blocks of eight participants in the workshop support group and web‐based support group, respectively. The control group is not randomised.

### Blinding

2.7

The clinical and health psychologists and psychotherapists, who conduct the assessments, are not blinded to the treatment arms.

### Statistical analysis plan

2.8

The treatment effect will be analysed by using mixed‐design ANOVAs. The time points will be included as within group factor, and the group (workshop support group vs. web‐based support group vs. TAU) will be included as between group factor. *t* tests for dependent and independent samples will also be used in order to explore differences between specific groups and specific time points.

Two analysis strategies will be applied to account for missing data: Intention‐to‐treat analysis will be used as the primary analysis strategy. If posttreatment or follow‐up data are missing, the last‐value‐put‐forward method will be used. Additionally, the analyses will be repeated by including completers only. Completers will be defined by attending more than 50% of the workshop sessions or web‐based modules. To analyse the potential effect of treatment moderators, additional ANOVAs will be calculated including patient's age and duration of illness as covariates.

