#### Primary hypothesis—Carers

1.3.1

Carers participating in the SUCCEAT intervention groups will report a greater reduction of distress (General Health Questionnaire: Linden et al., 1996) at postintervention (T1) than the carers in the control group.

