#### Primary hypothesis—Patients

1.3.2

Patients whose carers participate in the SUCCEAT intervention groups will show a greater reduction of ED symptoms (Eating Disorder Examination: Hilbert & Tuschen‐Caffier, 2006; Eating Disorder Inventory 2: Paul & Thiel, 2005) at postintervention (T1) than the patients in the control group.

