#### Study settings and locations where the data will be collected

2.2.2

Patients and carers will be recruited at different inpatient and outpatient centres with ED units, where they receive TAU. Carers and patients who meet the eligibility criteria are invited to participate in the study. Patients and carers both give their informed consent, and parents give their informed consent for children who are minors.

Carers and patients of the two SUCCEAT intervention groups will be recruited at the Medical University of Vienna, Department of Child and Adolescent Psychiatry, and by consultant child and adolescent psychiatrists and at different centres with ED units in adjacent federal states to Vienna. Patients and carers in the two intervention groups give their informed consent and complete the questionnaires at the Medical University of Vienna, Department of Child and Adolescent Psychiatry.

For the control group, patients and their carers will be recruited and receive TAU at three centres: at the Wilhelminenspital in Vienna, Department of Child and Adolescent Medicine, Inpatient and Outpatient Unit for Children and Adolescents; at the Clinical Centre Klagenfurt, Department of Neurology and Psychiatry for Children and Adolescents; and at the Parkland‐Clinic for Psychosomatic and Psychotherapy in Bad Wildungen, Germany. Patients and carers in the control group give their informed consent and complete the questionnaires at the recruiting site.

The interventions started in November 2014 and will continue approximately until April 2018. Follow‐up assessments for the remaining patients are expected to be completed by April 2019. The main ethics approval has been granted by the Medical University of Vienna Ethics Committee (1840/2013). Site‐specific ethics approvals are granted for all participating sites.

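### The only pairwise tool named in section 2.8, exploratory t tests, does not on its plain reading test a greater reduction than in the non-randomised TAU group

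*Protocol article*

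**What the plan says.** Both primary hypotheses concern a difference in change from T0 to T1 between the intervention groups and control. Carers in the intervention groups "will report a greater reduction of distress" (section 1.3.1), and their patients "will show a greater reduction of ED symptoms" (section 1.3.2).

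Section 2.8 names the main analysis: "The treatment effect will be analysed by using mixed‐design ANOVAs". Time points are the within factor, and "the group (workshop support group vs. web‐based support group vs. TAU) will be included as between group factor". It then adds that t "tests for dependent and independent samples will also be used in order to explore differences between specific groups and specific time points". The outcome variable of these t tests (level or change score) is not given, and no contrast of SUCCEAT with TAU within the ANOVA is named.

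On the comparator, section 2.6 states: "The control group is not randomised". Section 2.2.2 gives it its own recruiting sites: "For the control group, patients and their carers will be recruited and receive TAU at three centres". By section 2.1 the two intervention groups receive SUCCEAT on top of TAU, so every family in the study is under active treatment.

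**The concern.** A group-by-time interaction over three groups and three visits has four degrees of freedom. A significant result does not say which groups differ or between which visits. To conclude that SUCCEAT, or either format, reduced distress more than TAU, a further comparison is needed, and the t tests are the only one the article offers.

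On the plain reading, an independent-samples test compares two groups at one visit, so its null is equal levels. A dependent-samples test compares two visits in one group, so its null is no change in that group. Equal reduction in both groups is neither of these.

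With a randomised control, equal T1 levels would be a reasonable null. Here the control families come from other centres and may start at a different level, so a T1 difference can simply be a T0 difference carried along. All groups receive TAU, so improvement within SUCCEAT is to be expected even if SUCCEAT adds nothing. At stake is a statement that SUCCEAT beats TAU when it does not, or a real benefit hidden because SUCCEAT families started out worse.

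**Working it through.** **The plan's own figure.** Section 2.5 states 0.88 power with 40 per group, 5% level and a medium effect, for repeated-measures ANOVA without sphericity. Taking medium as f(V) = 0.25 (assumption), with 3 groups, 3 visits, N = 120 and the multivariate (Pillai) interaction test:
- df1 = (3 − 1)(3 − 1) = 4; s = min(2, 2) = 2; df2 = 2 × (120 − 3 − 2 + 2) = 234.
- λ = f² × N × s = 0.0625 × 120 × 2 = 15 gives power 0.884. With λ = f² × df2 = 0.0625 × 234 = 14.6 it is 0.875.

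The stated 0.88 is thus reproduced for the interaction. Some univariate variants also reach 0.88, but only with correlation or sphericity values that the article does not give. For dropout, 48 × 0.83 = 39.8, consistent with 40 per group.

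**Inputs for the illustration.** From the article: 40 completing per group, 5% level. Assumed, because the article gives no values: two-sided tests, SD 1 at each visit, baseline gap d of 0.3 or 0.5 SD, shared recovery r of 0.3 SD, T0–T1 correlation ρ of 0.3 to 0.7. The true change is equal in all groups, so every rejection read as a SUCCEAT effect is false.

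**Independent t test on T1 levels.** With equal change, the T1 gap equals the T0 gap d. Noncentrality = d × √(n/2), df = 2n − 2.

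| d | n = 40: noncentrality | Rejects | n = 48: noncentrality | Rejects |
|---|---|---|---|---|
| 0 | 0 | 5% | 0 | 5% |
| 0.3 | 1.34 | 26% | 1.47 | 31% |
| 0.5 | 2.24 | 60% | 2.45 | 68% |

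With both formats pooled against control (80 vs 40), noncentrality = d / √(1/80 + 1/40), which is 1.55 or 2.58, and the test rejects in 34% or 73%.

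**Dependent t test within one group.** Noncentrality = r × √n / √(2(1 − ρ)), df = n − 1, with r = 0.3 and n = 40:
- ρ = 0.3: 1.60, rejects in 35% (36% in a simulation of 8,000 trials)
- ρ = 0.5: 1.90, rejects in 46%
- ρ = 0.7: 2.45, rejects in 67%

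**Test on T0-to-T1 change between groups.** The expected contrast is (change in SUCCEAT) − (change in TAU) = 0. Both the constant gap d and the shared recovery r cancel. Simulated rejection is 4.5% to 5.5% in every null setting tried.

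**The case against.** The strongest reply is that the article already tests the right thing. It assigns the treatment effect to the mixed ANOVA, whose interaction is about differential change; the power calculation fits that interaction; and the t tests are introduced as additional and exploratory. This stands: the main analysis is not at fault, and the point is confined to the pairwise follow-up.

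A reader might infer that the plan commits itself to t tests on levels. It does not. An independent t test on change scores fits the same words and would test the hypothesis directly. What remains is that nothing in section 2.8 says so, and the plain reading of groups and time points leads elsewhere.

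A reader might also infer that the plan will claim efficacy from a result significant in SUCCEAT but not in control. No such rule is stated, and pooling the two formats would not be the main cause of that pattern. With r = 0.3, ρ = 0.5 and 40 in each group it already arises in 0.46 × 0.54 = 25% of trials.

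Nor does the problem extend to workshop versus web. Those groups are randomised, so a T1-level comparison between them is valid in expectation.

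Finally, it could be said that such detail belongs in a fuller analysis plan. But the section names a pairwise tool, and on its plain reading that tool does not match the stated hypotheses. That is more than a missing detail.

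**Conclusion.** The point holds for the pairwise comparisons with TAU and no further. Read plainly, the named t tests do not test a greater reduction. Against a non-randomised control they can reject because of a baseline gap (about 26% at 0.3 SD and 60% at 0.5 SD, 40 per group) or shared recovery (about 35% to 67% at 0.3 SD), where a test on change stays near 5%.

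These rates are illustrations. The gap, the recovery and the correlation are assumptions, and with no baseline gap the T1-level test also stays at 5%. The 5% for change scores rests on equal true change: such a contrast removes a constant baseline gap, but not regression to the mean or different natural courses between centres. The tests' exploratory label limits the harm but does not remove it, since no other pairwise comparison is named.

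**What to change.** In section 2.8, state that the comparisons of SUCCEAT (pooled, workshop, web) with TAU are made as group-by-time contrasts from the mixed model for T0 to T1 and T0 to T2, or as independent t tests on the corresponding change scores, with 95% confidence intervals. State also that within-group t tests and T1-level t tests against TAU are descriptive and will not support a claim that SUCCEAT is better than control. Workshop versus web can be left as it is.

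The cost is one or two sentences, with the same data and software. The price is that a significant improvement within a SUCCEAT group can no longer be offered as evidence of an effect.

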#### Secondary hypotheses

1.3.3

There will be differences in improvement of carers' and patients' outcome variables between the two SUCCEAT intervention groups (workshop support groups vs. web‐based support groups).Carers participating in the SUCCEAT intervention groups will report a greater reduction of burden (Eating Disorder Symptom Impact Scale: Sepulveda, Whitney, et al., 2008), as well as psychiatric symptomatology (Symptom Checklist 90: Franke, 2002), anxiety (State–Trait Anxiety Inventory: Laux et al., 1981), depression (Beck Depression Inventory II: Hautzinger et al., 2006), HEE (Family Questionnaire: Wiedemann et al., 2002), and unmet needs (Carers' Needs Assessment Measure: Graap et al., 2005) at postintervention (T1) than the carers in the control group. Further, they will report a greater increase of motivation to change (University of Rhode Island Change Assessment Scale: Hasler et al., 2003), positive experiences of caregiving (Experience of Caregiving Inventory: Szmukler et al., 1996), and caregiving skills (Caregiver Skills: Hibbs, Rhind, Salerno, et al., 2015) at postintervention (T1) than the carers in the control group.Carers will report acceptability and satisfaction with the SUCCEAT intervention (SUCCEAT Treatment Satisfaction Questionnaire).Patients whose carers participate in the SUCCEAT intervention groups will show a greater reduction of behavioural and emotional problems (Youth Self‐Report: Arbeitsgruppe Deutsche Child Behavior Checklist, 1998) and perceived HEE (Family Emotional Involvement and Criticism Scale: Kronmüller et al., 2001), as well as a greater increase of Body Mass Index, quality of life (Health‐Related Quality of Life Questionnaire for Children and Adolescents: Ravens‐Sieberer & Bullinger, 1998a, 1998b), and motivation to change (Anorexia Nervosa Stages of Change Questionnaire: Rieger et al., 2002) at postintervention (T1) than the patients in the control group.Outcome variables of the carers participating in the SUCCEAT intervention groups and their patients will remain stable at follow‐up (T2) compared with postintervention (T1).The costs of support (Client Sociodemographic and Service Receipt Inventory: Roick et al., 2001) will be lower for carers (and their patients) participating in the SUCCEAT intervention groups at postintervention (T1) and at follow‐up (T2) than for the carers (and their patients) in the control group.

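### Last value carried forward in the primary analysis distorts the T1 effect, in a direction set by the dropout pattern, and pulls the T1–T2 change towards zero

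*Protocol article*

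**What the plan says.** Section 2.8 (Statistical analysis plan) of the protocol article makes intention-to-treat the primary strategy. For missing posttreatment or follow-up data it fixes that the "last‐value‐put‐forward method will be used". The analyses are mixed-design ANOVAs over time and group, with dependent and independent t tests. The only other handling of missing data is a repeat in completers, defined as those attending more than half of the sessions or modules.

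Three other places decide what this rule affects:

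- The primary carer hypothesis (section 1.3.1) is that SUCCEAT carers "will report a greater reduction of distress" at T1 than controls. Section 1.3.2 says the same for patients' eating disorder symptoms. Both concern change from T0 to T1.
- A secondary hypothesis (section 1.3.3) is that outcomes in the SUCCEAT groups "will remain stable at follow‐up (T2) compared with postintervention (T1").
- Section 2.5 gives a single dropout figure ("We expect a dropout rate of about 17" per cent), not split by arm or visit. Assessments (section 2.4) fall before the intervention, "after 3 months (postintervention, T1), and 1 year after the intervention (follow‐up, T2").

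**The concern.** Carrying the last value forward assumes that a family stopped changing when it was last seen. At T1 that means no change since baseline, although every group receives treatment as usual and may well improve. Each group's mean change is then scaled down by its own missing share, and the difference between groups moves with any imbalance in dropout.

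Equal dropout cannot be taken for granted. The control group is not randomised (section 2.6). It is recruited and assessed at three other centres, one of them in Germany, whereas SUCCEAT families complete their questionnaires at one Vienna department (section 2.2.2). The two SUCCEAT formats also ask different things of families.

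At T2 the filled value equals the T1 value, which is the result that the stability hypothesis predicts. At stake are the estimates for both primary hypotheses and for the claim that gains last.

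**Working it through.** **The plan's own figures.** Section 2.5 states the design as "at a 5% significance level with 0.88 power", "carers of 40 patients per group are needed to detect medium effects", and "48 patients per treatment arm, resulting in a total sample size of 144". Taking medium as f = 0.25 (my assumption), with 3 groups, 3 time points and N = 120, the multivariate group-by-time test has noncentrality f² × N × s = 0.0625 × 120 × 2 = 15 on 4 and 234 degrees of freedom. Its power is 0.884, against 0.88 stated. For dropout, 48 × 0.83 = 39.84, so 48 per arm leaves about 40. The 17% is thus a planned loss of about 8 families per arm.

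**T1 effect.** Let g be the true mean improvement from T0 to T1 (SD units) and d the share missing T1, with I for SUCCEAT (96 families) and C for control (48). Assume missingness unrelated to outcome, the case kindest to the method. Filled families contribute zero change, so:

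- expected estimate = gI(1 − dI) − gC(1 − dC)
- bias = gC·dC − gI·dI

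Two unequal splits keep the overall loss at 17%:

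- 22%/7%: (0.22 × 96 + 0.07 × 48)/144 = 24.48/144 = 0.17
- 10%/31%: (0.10 × 96 + 0.31 × 48)/144 = 24.48/144 = 0.17

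For improvements of 1.0 v 0.5 SD:

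- 17%/17%: 0.83 − 0.415 = 0.415
- 22%/7%: 0.78 − 0.465 = 0.315
- 10%/31%: 0.90 − 0.345 = 0.555

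The same formula for other assumed improvements gives:

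| Improvement, SUCCEAT v control | True effect | 17%/17% | 22%/7% | 10%/31% |
|---|---|---|---|---|
| 1.0 v 0.5 | 0.50 | 0.415 | 0.315 | 0.555 |
| 0.8 v 0.3 | 0.50 | 0.415 | 0.345 | 0.513 |
| 0.5 v 0 | 0.50 | 0.415 | 0.390 | 0.450 |
| 0.5 v 0.5 | 0 | 0 | −0.075 | +0.105 |

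A positive sign favours SUCCEAT. With equal dropout the estimate is the true effect × (1 − d), whatever the improvements. If 17% is the cumulative loss to T2, fewer are missing at T1. With half of it (8.5%), for example, the estimate is 0.50 × 0.915 = 0.4575.

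**T1–T2 change.** If a share m has T1 but not T2, the expected estimate is the true change × (1 − m). For a true loss of 0.30 SD and m = 0.17 this is 0.30 × 0.83 = 0.249.

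The standard error shrinks too, because the filled zeros count as data. In a simulation of 48 families with 8 filled and SD of change 1, it averaged 0.132, against 0.157 from the 40 observed changes, so it was about 16% too small. The 95% interval excluded the true relapse on the favourable side 5.7% of the time, against 2.4% with observed data.

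**Power of the paired test.** Estimate and standard error shrink together (0.25/0.132 = 1.89; 0.30/0.157 = 1.91), so the test barely moves. Simulating 96 families with a true loss of 0.30 SD gave power of 0.759 with carried-forward values and 0.760 with observed data only at 17% missing. At 34% missing the figures were 0.655 and 0.656.

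**The case against.** The strongest reply has four parts.

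- **The sizes are not in the document.** The article gives no change scores and no dropout by arm or visit. This stands: every size above is conditional, and the table shows that even the sign of the bias depends on the inputs. What does not depend on them is that filled families are assigned zero change.
- **A reader might infer that stability is built in, or that the method hides relapse from the test.** Neither is supported. Only families missing T2 are set to no change, so at 17% missing a 0.30 SD loss still appears as 0.25 SD. The paired test's power is the same with and without the filled values. The damage is to the estimate and its interval.
- **A reader might infer that controls will drop out differently because they receive nothing.** Section 2.3.2 says otherwise: controls receive conventional carers' support and treatment as usual. The case for unequal dropout rests on the nonrandomised allocation, the different sites and the different formats.
- **An article may leave detail to a full analysis plan.** That covers the absence of a stability margin for a secondary hypothesis, which is not counted as an error here. It does not cover the method for missing data, which the article states outright.

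Nor can the method be defended as conservative. With 10%/31% missing and improvements of 1.0 v 0.5 SD it inflates the effect, and it can create one where none exists. The completer repeat does not offset it: it selects on attendance rather than on available outcome data, so filled values can remain, and attendance has no meaning for controls.

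**Conclusion.** The concern holds in this form. The stated primary handling of missing data biases the T1 comparison whenever the groups improve and lose families, except where the two losses happen to cancel (gC·dC = gI·dI).

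For a true 0.50 SD effect the estimate is 0.415 SD if the full 17% is missing equally at T1, with less shrinkage if 17% is cumulative to T2. At the same overall loss it ranges from 0.315 to 0.555 SD over the splits and improvements tried. Under no effect, with both groups improving by 0.5 SD, it is −0.075 or +0.105 SD.

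The T1–T2 change is pulled towards the predicted stability in proportion to the share missing T2, with a standard error that is too small. These sizes assume missingness unrelated to outcome, and the change scores and dropout splits are mine.

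**What to change.** In section 2.8, replace last value carried forward with a likelihood-based mixed model for repeated measures that takes T0, T1 and T2 all as outcomes, with group, time and group-by-time terms, fitted to all observed data. Under missing at random it needs no imputation, and families with only T0 stay in the model.

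T0 should be an outcome rather than a covariate for two reasons. As a covariate it drops families with no later value. With a nonrandomised control it may also target a different quantity from the greater reduction named in the primary hypotheses. The model does not remove confounding from the nonrandomised control, which is a separate matter.

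Add a missing-not-at-random sensitivity analysis, such as delta-adjusted multiple imputation, and keep carrying forward at most as a further sensitivity analysis. Report the T1–T2 change from the model with its 95% confidence interval, and do not read non-significance as stability. Any margin is for the investigators to state in advance.

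The cost is revised wording, modest programming, and slightly wider intervals that reflect the data actually collected. No extra families or assessments are needed.

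### The moderator analysis names age and illness duration as covariates but no interaction with group, so read in the usual way it cannot test moderation

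*Protocol article*

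**What the plan says.** Section 2.8 (Statistical analysis plan) sets out mixed-design ANOVAs. Of time it says "The time points will be included as within group factor". Group, with levels workshop, web-based and treatment as usual (TAU), "will be included as between group factor". That model carries no covariates.

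Moderators get one sentence, at the end of the section: "To analyse the potential effect of treatment moderators, additional ANOVAs will be calculated including" the patient's "age and duration of illness as covariates". It names no product of age or duration with group, or with group and time, and gives no subgroup contrast. No other section of the article describes a moderator analysis.

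Section 2.5 gives the planned size: "carers of 40 patients per group are needed", "at a 5% significance level with 0.88 power", for the carers' distress outcome. Section 2.6 states that the control group is not randomised.

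**The concern.** A moderator is a variable across whose values the treatment effect differs. In a model for change over time, that is a group by time by covariate interaction. A variable entered as an ANOVA covariate is conventionally given one slope shared by all groups. Its test asks whether age or duration predicts the outcome. If a time by covariate term is also fitted, the test asks whether the covariate predicts change, still to the same degree in every group. Either way, the difference in slopes between groups is fixed at zero, and that difference is the quantity the stated aim asks about.

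What is at stake is the answer to whether benefit varies with age or illness duration. The question is a natural one here, because section 2.2.1 admits patients from 10 to 19 years and the introduction presents the inclusion of patients under 13 as new. A common-slope model gives no evidence on it in either direction.

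**Working it through.** **1. The plan's own figure.** Section 2.5 states power 0.88 with 40 per group for "patients per group are needed to detect medium effects", without a number for the effect. Assume Cohen's f = 0.25, three groups, three time points and the multivariate repeated-measures test of the group by time interaction: N = 3 × 40 = 120, s = min(3 − 1, 3 − 1) = 2, numerator df = 2 × 2 = 4.
- λ = f² × N × s = 0.0625 × 120 × 2 = 15.0, power 0.884.
- λ = f² × (N − 3) × s = 0.0625 × 117 × 2 = 14.6, power 0.875.

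The stated 0.88 is reproduced. It concerns the primary outcome and says nothing about power for a moderator interaction. Nothing below changes the sample size.

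**2. The two models.** Let y be the change from T0 to T1, x the standardised covariate and g the group.
- Covariate model: y = α_g + βx + error. One β for all groups.
- Moderation model: y = α_g + β_g x + error. Moderation means that the β_g differ.

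The first model is the second with all β_g set equal, so a test of β in it carries no information on whether they are equal. With two time points, group by covariate on change is the same test as group by time by covariate in the mixed ANOVA.

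**3. Illustration.** Simulated change scores, 40 per group, residual SD 1, α = 0.05, 4,000 runs per case. Every slope is an assumption; none comes from the protocol. Slopes are listed as control / workshop / web-based.

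| Case | Slopes | Covariate term significant | Group × covariate significant |
|---|---|---|---|
| (a) Prognostic only | 0.4 / 0.4 / 0.4 | 98.9% | 4.9% |
| (b) Moderation averaging to zero | −0.4 / 0.2 / 0.2 | 5.7% | 76.7% |
| (c) Moderation not averaging to zero | 0 / 0.4 / 0.4 | 79.6% | 41.0% |
| (d) No effect | 0 / 0 / 0 | 4.8% | 4.8% |

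In (b) the mean slope is (−0.4 + 0.2 + 0.2)/3 = 0, so the common slope has nothing to detect. In (c) it is (0 + 0.4 + 0.4)/3 = 0.27, so the covariate term is often significant. It is also significant in (a), where there is no moderation, so significance does not separate the two situations.

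**4. Other assumed slopes.** A separate set of 1,500 runs compared 80 intervention with 40 control. With a prognostic slope of 0.5 and no moderation, the covariate term was significant in 99.9% and the interaction in 4%. With a slope difference of 0.6 averaging to zero, the figures were 6% and 85%. The pattern is the same.

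**5. Power of the correct test.** The interaction test has 41.0% power in (c) and 76.7% in (b). In (c) the slopes differ by 0.4 between the control group and both interventions, and power is still below one half.

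**The case against.** The strongest reply is that the sentence lists the variables to be entered and not every model term. It does not say that they enter only as covariates, and it excludes no interaction. A condensed article may leave the exact terms of an additional analysis to a fuller plan. The group by time interaction, on which the primary hypotheses rest, is not named either, yet nobody would say it is absent.

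The first part stands: the text is silent on interactions and does not rule them out. The parallel does not hold. A mixed-design ANOVA with a within factor and a between factor contains their interaction by construction, whereas entering a variable as a covariate does not by convention add its product with group. Nor is this mere missing detail, because the sentence pairs an aim with a method that, as usually understood, does not serve it. If a fuller plan has the interaction, the sentence still describes it wrongly.

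A reader might also infer that the plan will label prognostic factors as moderators. The document does not support that. It gives no decision rule for moderators and nowhere says that a significant covariate term will be read as moderation. That reading is a risk of the wording and not a stated rule.

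The objection to the simulation is also partly right. That a main-effect test finds main effects and an interaction test finds interactions is true by construction, and the contrast in case (b) depends on slopes that cancel. The rates illustrate the point and do not predict this trial's error rates.

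**Conclusion.** The point holds in a limited form. Read in the usual way, the stated moderator analysis adjusts for age and duration or shows them to be prognostic, and cannot show whether they modify the treatment effect. This follows from the model's structure and does not depend on the simulated slopes. It does rest on the conventional reading of a covariate as having a common slope.

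The consequences are modest. The analysis is additional, moderation appears in none of the hypotheses in section 1.3, and neither the primary conclusions nor the sample size is affected. The sentence should be corrected because, followed as written, the analysis would not answer its own question.

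Two limits remain after correction. Interaction power is likely to be low, as case (c) illustrates. And because the control group is not randomised, an interaction against TAU stays open to confounding; workshop versus web-based is the only randomised contrast.

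**What to change.** Replace the moderator sentence in section 2.8, or clarify it in the statistical analysis plan, so that it states the following:

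- Moderation is tested by the group × time × age and group × time × illness-duration interactions, with both covariates continuous and centred. For T1, the group × covariate term on the baseline-adjusted outcome serves the same purpose. Choose one form in advance, since the two need not give identical estimates when one group is not randomised.
- Results are reported as interaction estimates with 95% confidence intervals and labelled exploratory.
- Models with age and duration as covariates alone are described as adjustment, not as moderator analyses.
- Power for these interactions is likely to be low, so a non-significant result is not evidence that the effect is uniform.
- Interactions for workshop versus web-based are presented separately from those against TAU, with a note that the latter may be confounded.

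The cost is a few sentences. Both variables are already planned for the analysis, so no new data are needed.
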